**Exploratory endpoints:**

1. Change in SARS-CoV-2 RNA level (Polymerase chain reaction, Cycle Threshold value) in oral or nose/throat swab samples at days 3, 14, 28, hospitalisation and 180 after randomisation (cohort 2 only)
2. Change in anti-SARS-CoV-2 spike antibody levels in blood at days 3, 14, 28 and hospitalisation after randomisation

3. SARS-CoV-2 whole-genome sequence analysis in oral or nose/throat swab samples at day 1, 28, hospitalisation and day 180 after randomisation
4. Proportion and clinical characteristics of patients with cultivable virus at day 28, hospitalisation and day 180
5. Virus sequence variation and cultivability over time, overall and in individuals receiving vs not receiving CP

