### **II-2. WHY IS THIS RESEARCH IMPORTANT?**

People in clinically vulnerable groups will continue to be exposed to SARS-CoV-2 during future waves, at hospital visits, in the community and at home and so continue to be at risk of severe disease and death. Early CCP may reduce morbidity and mortality from COVID-19 pneumonia and avoid complications such as secondary bacterial infections and need for hospitalisation. In addition, CCP may be of particular benefit in people in whom a SARS-CoV-2 vaccine may not elicit effective immune responses, such as older people, those with congenital immunodeficiency or the large number of COVID-19 Core protocol

patients who are immunocompromised due to underlying disease and/or immunosuppressive therapy.

Faster resolution of COVID-19 may avoid delays to life-saving treatments, such as stem cell transplantation. Antibody therapies in early COVID-19 have the potential to improve quality of life and reduce long-term COVID-19 symptoms. Wider benefits may include reduced burden on limited healthcare resources by reducing hospital admissions for COVID-19 and increasing resources for urgent, non-COVID-19 work in hospitals.

Faster viral clearance in patients treated early will reduce the period of infectivity, conferring particular benefit for immunocompromised people in whom viral shedding can be prolonged, people on haemodialysis, who require frequent visits to healthcare facilities, and those in residential settings with high risk for outbreaks e.g. care homes. Demonstration of CCP effectiveness in outpatient settings may influence future policy surrounding lockdown measures and inform health resource planning. Importantly, early in a pandemic, or in case of the emergence of an immuno-resistant variant, CCP may be the only passive immunotherapy approach readily available. Also, when available, access to monoclonal antibodies or hyperIg may be limited by manufacturing or costs issues. It already has been observed that SARS-CoV-2 spike mutations in newly emerging variants confer resistance against monoclonal antibodies limiting their potential benefit.

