### **II-3-3. Covid-19 convalescent plasma to treat COVID-19**

COVID-19 convalescent plasma (CCP) has been, and still is assessed in a large number of clinical trials, mainly in hospitalized patients. By and large, most trials performed in hospitalized patients have so far been unable to demonstrate a beneficial effect of convalescent plasma, while often offering evidence that early to very early transfusion of high titre CCP may be advantageous. Accordingly, and as mentioned earlier, a recent randomized study exhibited a favorable effect of very early administration of high-titre CCP in vulnerable patients. Libster et al. randomized vulnerable older adult patients within 72 h after onset of mild COVID-19 symptoms to receive CCP with high IgG titres against SARS-CoV-2 or placebo. The primary end-point was the occurrence of severe respiratory disease. A total of 160 patients underwent randomization. In the intention-to-treat population, severe respiratory disease developed in 13 of 80 patients (16 %) who received CCP and 25 of 80 patients (31 %) who received placebo (relative risk, 0.52; 95 % confidence interval [CI], 0.29 to 0.94; P =0.03), with a relative risk reduction of 48 %. A modified intention-to-treat analysis that excluded 6 patients who had a primary end-point event before infusion of CCP or placebo showed a greater effect size (relative risk, 0.40; 95 % CI, 0.20 to 0.81). Notably, an Ab dose effect was observed with a 73 % reduction in disease worsening in recipients of CCP with a titre at or above the median concentration versus 31,4% in recipients of CCP with a titre below the median concentration. No adverse events were reported.

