#### **III-3. Exploratory objectives**

The study also aims to:

- Analyse the effect of convalescent plasma on SARS-CoV-2 viral load.
- Describe the course of anti-SARS-CoV-2 spike antibody levels in blood (provisional).
- Analyse the SARS-CoV-2 whole genome sequence.
- Determine whether persistently-infected immunosuppressed individuals are a source of infectious viral variants.
- Analyse the association between receipt of CCP and development of infectious SARS-CoV-2 viral variants.

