| Oxygenation                                          |                                             |                |                | X              | X              | X                                                      |             |                |
| Clinical Progression Scale                           |                                             | X              | X              | X              | X              | X                                                      |             |                |
| QoL and long COVID
Questionnaires                 |                                             | X              |                |                | X              |                                                        |             | X              |
| Adverse event recording                              |                                             | X              | X              | X              | X              | X                                                      | X           | X              |
| Laboratory analyses                           |                                             |                |                |                |                |                                                        |             |                |
| SARS CoV 2 RT-PCR in nose and
throat swabs/saliva | X                             | X              | X  | X  | X  | X                                                      |             | X  |

|                                                                                 |                |                  |                |                |                  |                  |  |                  |
|---------------------------------------------------------------------------------|----------------|------------------|----------------|----------------|------------------|------------------|--|------------------|
| SARS CoV 2 sequencing (whole genome sequencing)                                 | X  | X                |                |                | X    | X    |  | X    |
| SARS CoV 2 isolation from nose and throat swab/saliva (cohort 2 only, optional) |                | X  |                |                | X  | X  |  | X  |

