| SARS CoV 2 antibody in serum                                                    | X              | X                | X  | X  | X    | X                |  |                  |
| Biochemistry bloods                                                 |                | X                |                | X  |                  | X                |  |                  |
| Haematology bloods                                                  |                | X                |                | X  |                  | X                |  |                  |
| Pregnancy test (in females of childbearing potential only)                      | X              |                  |                |                |                  |                  |  |                  |
| Serum for biobank (optional)                                                    |                | X    |                | X  | X    | X    |  |                  |
| Plasma for biobank (optional)                                                   |                | X    |                | X  | X    | X    |  |                  |
| EDTA sample (for isolation of immune cells) for biobank (optional)              |                | X    |                | X  | X    | X    |  |                  |

 For individuals with no RT PCR or Antigenic test result in the preceding 7 days

 Cohort 2; in cohort 1 only if the patient's have not been tested negative in the SARS-CoV-2 PCR before.

 Urea, Electrolytes, Liver Function Tests (ALT, AST), Creatinine, calcium, phosphate, glucose, C-reactive protein (CRP). LDH, ferritin, IL-6 (optional)

 Full Blood Count (neutrophils/total lymphocyte counts, platelets), Prothrombin, Activated partial thromboplastin time (aPTT), fibrinogen, D dimer, G&S

 Visit "hospitalization" on the day of hospitalization and/or start of supplementary O2 (+ 2 days) (only if this event occurs up to day +28).

 if viral load still sufficient to perform sequencing or virus isolation

 between screening and administration of CCP (D1)

 not mandatory

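### The variant and culture comparison is worded by plasma received, and the assays depend on viral load: define it by allocated arm with a stated denominator

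*Protocol*

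**What the plan says.** **How the groups are defined.** Protocol III-4 sets the endpoint as "Virus sequence variation and cultivability over time, overall and in individuals receiving vs not receiving CP", and the list of exploratory outcomes in X-3 repeats it. The matching objective in III-3 is "Analyse the association between receipt of CCP and development of infectious SARS-CoV-2 viral variants". All three places speak of receipt of plasma. Below its list, however, X-3 says that the exploratory biomarkers are summarised by treatment group and collection time. X-1-2 states the intention-to-treat principle and places patients in the group given by randomisation, although the sentence that names the ITT population applies it to efficacy analyses.

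**Which samples are assayed.** Footnote 6 of Table 3 makes an assay conditional: "if viral load still sufficient to perform sequencing or virus isolation". It is attached to sequencing at D28, hospitalisation and D180, and to isolation at D1, D28, hospitalisation and D180. Sequencing at D1 does not carry it. Isolation is restricted further: "SARS CoV 2 isolation from nose and throat swab/saliva (cohort 2 only, optional)". Footnote 2 limits follow-up PCR: it applies to cohort 2, and "in cohort 1 only if the patient's have not been tested negative in the SARS-CoV-2 PCR before".

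**What plasma is expected to do.** III-3 lists as an objective "Analyse the effect of convalescent plasma on SARS-CoV-2 viral load". II-2 states the expected direction: "Faster viral clearance in patients treated early will reduce the period of infectivity".

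**Why the endpoint exists.** II-5-1 names selection of resistant variants as a possible risk of passive immunotherapy, especially in immunosuppressed patients who carry virus for a long time.

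**The concern.** There are two separate difficulties.

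1. Grouping by plasma received gives up the randomised comparison. VIII-1 keeps every randomised patient in the study whether or not the allocated treatment is given, so receipt and allocation can differ, and the reason for not receiving plasma may be related to prognosis.
2. If the comparison is made among sequenced or cultured samples, patients enter it because they still have enough virus. That is a consequence of treatment if plasma works as the protocol expects. The patients left in the plasma arm may then be a harder-to-clear group than those left in the control arm.

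At stake is the trial's reading of a risk it names itself. Plasma could look neutral or unfavourable among assayed samples while fewer plasma patients overall harbour a new variant. No primary, secondary or interim decision depends on this.

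**Working it through.** The plan states no figure for this endpoint, so there is none to reproduce. The check has two parts.

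**Part 1: the texts side by side.**

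| Place | Grouping |
|---|---|
| III-3, objective | receipt of plasma |
| III-4, endpoint | receiving or not receiving |
| X-3, exploratory list | receiving or not receiving |
| X-3, sentence below the list | treatment group |
| X-1-2 | group assigned by randomisation |

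The first three and the last two cannot both govern the same comparison unless everyone receives exactly what was allocated.

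**Part 2: what the viral-load condition can do.** For one arm, let half the patients be profoundly immunosuppressed (type 1) and half not (type 0). Let p1 and p0 be the probabilities of enough virus to sequence at the visit, and q1 and q0 the probabilities of a new variant given enough virus.

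- Fraction sequenced: S = 0.5·p1 + 0.5·p0
- Fraction of all randomised with a variant: V = 0.5·p1·q1 + 0.5·p0·q0
- Share among the sequenced: V / S

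With T for plasma and C for control, the two ratios are linked:

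(V_T/S_T) / (V_C/S_C) = (V_T/V_C) / (S_T/S_C)

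They therefore differ whenever plasma changes the fraction that can be sequenced.

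Inputs: 170 per arm comes from X-2 and is used only for scale, with everyone sampled. **All rates are assumptions; the protocol gives none.** q1 = 0.40 and q0 = 0.10 in both arms, so plasma has no effect on variants once virus persists.

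Scenario A in full:

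- Control (p1 = 0.40, p0 = 0.10): S = 0.25, or 42.5 of 170. V = 0.5×0.40×0.40 + 0.5×0.10×0.10 = 0.085. V/S = 34.0%.
- Plasma (p1 = 0.30, p0 = 0.02): S = 0.16, or 27.2 of 170. V = 0.5×0.30×0.40 + 0.5×0.02×0.10 = 0.061. V/S = 38.1%.
- Among the sequenced: 38.1/34.0 = 1.12. Per randomised patient: 0.061/0.085 = 0.72. Check: 0.72 / (0.16/0.25) = 1.12.

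| Scenario | Control p1/p0 | Plasma p1/p0 | Sequenced of 170, C vs T | Ratio among sequenced | Ratio per randomised |
|---|---|---|---|---|---|
| A | 0.40/0.10 | 0.30/0.02 | 42.5 vs 27.2 | 1.12 | 0.72 |
| B | 0.50/0.20 | 0.45/0.02 | 59.5 vs 40.0 | 1.23 | 0.83 |
| C | 0.40/0.10 | 0.15/0.09 | 42.5 vs 20.4 | 0.85 | 0.41 |
| D, same relative clearance | 0.40/0.10 | 0.20/0.05 | 42.5 vs 21.2 | 1.00 | 0.50 |
| E, mild | 0.40/0.10 | 0.32/0.05 | 42.5 vs 31.4 | 1.06 | 0.78 |

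The ranges are 0.85 to 1.23 among the sequenced and 0.41 to 0.83 per randomised patient. A, B and E fall on opposite sides of 1; C does not. In D the ratio among the sequenced recovers the assumed null effect given persistence, while the per-randomised ratio is 0.50.

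**The case against.** **Receipt may simply mean arm.** In a two-arm trial of plasma against no plasma, the wording may be shorthand, and the treatment-group sentence in X-3 supports that reading. A reader might infer that the sponsor has fixed an as-treated analysis. The documents do not support more than a mismatch that needs reconciling. The mismatch stands, because three places agree on receipt.

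**The viral-load footnote is a laboratory limit.** A sample with too little virus cannot be sequenced, and no passage restricts the analysis to assayed patients. A reader might infer that the comparison is already selected. It is not: the protocol text leaves the denominator open. The point is conditional on a comparison among assayed samples, and detail may properly sit in the SAP.

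**Persistence is partly the question.** III-3 also asks whether persistently infected immunosuppressed patients are a source of infectious variants. For that objective, results among patients who still carry virus are relevant and should stay.

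**How many patients would change group?** II-3-3 reports that the cited trial of early plasma "excluded 6 patients who had a primary end-point event before infusion of CCP or placebo", from 160 randomised. A reader might scale this to the present trial. The text neither splits the six by arm nor says they went without the infusion, so it gives no estimate of patients moving to the comparator.

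**Is the result uninterpretable?** A reader might conclude that neither its size nor its sign could be read. Scenario D shows otherwise: without differential clearance, the ratio among the sequenced is undistorted for the effect given persistence.

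**Conclusion.** The point holds in a limited form. The protocol words the between-group comparison by plasma received and elsewhere by assigned group; taken literally, the former is not a randomised comparison. Separately, follow-up sequencing and all isolation depend on a quantity that plasma is expected to lower, so a comparison confined to assayed samples answers a different question from one per randomised patient. Under the assumed rates the ratios are 0.85 to 1.23 against 0.41 to 0.83, and 1.00 against 0.50 with uniform relative clearance. Reversal of direction requires clearance to differ by patient type, which the documents neither assert nor exclude. These figures show what is possible and do not predict the trial's result.

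Severity is low. The endpoint is exploratory, and the primary and secondary analyses are untouched. It is worth settling because it bears on a risk named in II-5-1 and costs only wording.

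**What to change.** 1. In III-3, III-4 and X-3, make the between-group comparison by allocated arm, within each cohort.
2. For that comparison, use as denominator the randomised patients sampled at the visit: both cohorts as sampled for sequencing, cohort 2 only for culture.
3. Count a PCR-negative sample, or one with too little virus, as no cultivable virus or no new variant detected. In cohort 1, treat a swab omitted under footnote 2 after an earlier negative PCR in the same way; otherwise the denominator is itself selected on clearance.
4. Treat a sample with adequate load that was not assayed because the assay is optional as missing, not negative.
5. Report the number assayed per arm beside each result.
6. Keep results by plasma received and among assayed samples as descriptive, including those for the objective on persistently infected patients. Hospitalisation-day samples exist only in patients who were hospitalised or started oxygen, so comparisons there also remain descriptive.

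The cost is wording only, with no extra sample or assay. The downside is that a few low-load samples that might have grown, or carried a variant, are scored negative. A sensitivity analysis can bound this.

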**Table 2. 10-point WHO Progression scale**

| Patient state                  | Descriptor                                                                                                               | Score |
|--------------------------------|--------------------------------------------------------------------------------------------------------------------------|-------|
| Uninfected                     | Uninfected; no viral RNA detected                                                                                        | 0     |
| Ambulatory                     | Asymptomatic; viral RNA detected                                                                                         | 1     |
|                                | Symptomatic; independent                                                                                                 | 2     |
|                                | Symptomatic; assistance needed                                                                                           | 3     |
| Hospitalised: moderate disease | Hospitalised; no oxygen therapy*                                                                                         | 4     |
|                                | Hospitalised; oxygen by mask or nasal prongs                                                                             | 5     |
| Hospitalised: severe disease   | Hospitalised; oxygen by NIV or high flow                                                                                 | 6     |
|                                | Intubation and mechanical ventilation, pO 2 /FiO 2 ≥150 or SpO 2 /FiO 2 ≥200 | 7     |
|                                | Mechanical ventilation pO 2 /FiO 2 <150 (SpO 2 /FiO 2 <200) or vasopressors  | 8     |
|                                | Mechanical ventilation pO 2 /FiO 2 <150 and vasopressors, dialysis, or ECMO                        | 9     |
| Dead                           | Dead                                                                                                                     | 10    |

ECMO=extracorporeal membrane oxygenation. FiO2=fraction of inspired oxygen. NIV=non-invasive ventilation. pO2=partial pressure of oxygen. SpO2=oxygen saturation. \*If hospitalised for isolation only, record status as for ambulatory patient.

## **IV. STUDY DESIGN**

### **IV-1. Overall design**

COVIC-19 is a multicentre international, randomised, open-label adaptive superiority phase III trial to evaluate the efficacy and safety of COVID-19 convalescent plasma in the treatment of COVID-19. It is conducted in a harmonized approach in different countries in Europe.

The study is randomizing adult COVID-19 patients to one of two arms (1:1 ratio): standard of care or standard of care and very high neutralizing Ab titre convalescent plasma. Randomization will be stratified by centre and by patient cohort. The control group will receive 'standard care' therapy. Neither blinding nor placebo will be used to avoid unnecessary intravenous access.

Standard of care therapy may include anti-SARS-CoV-2 specific medication listed as authorized in a dedicated appendix. Centres should ensure that medications used as standard of care are used similarly for patients in both treatment arms.

Participating patients will be included in 2 cohorts of vulnerable patients (cohort 1: unvaccinated elderly ( $\geq 70$  years) and younger with comorbidities (cohort 1:  $< 70$  with comorbidities), cohort 2: immunosuppressed patients).

All subjects will undergo a series of efficacy and safety assessments, including laboratory assays. Subjects will be assessed at baseline, and at Days 3, 14, 28, 90 and 180.

Nasopharyngeal swabs (NP) or lower respiratory tract samples will be obtained at D1 (pre-treatment), and at D3, D14, D28 and D180 (and monthly in case of positivity until of clearance) for cohort 2 and on the day of hospitalization (if applicable).

Blood samples will be obtained at D1, D14 and D28 and on the day of hospitalization (if applicable).

### **IV-2. Rationale for study design**

The COVIC-19 study will include two distinct cohorts: firstly, unvaccinated elderly and younger patients with co-morbidities, and secondly, immunocompromised patients. This distinction is justified in particular by the differences between these two groups with regard to the characteristics of the COVID-19 disease, differences accentuated by the effects of the vaccination, significant in the 1st cohort, much less so in the 2nd cohort. The two cohorts will be analyzed separately.

The COVIC-19 study will be carried out in 2 stages:

- A 1st step with the objective of confirming or not the data of Libster et al in each of the cohorts (50% reduction of a risk of a 30% aggravation rate) with a power of 90%, an alpha risk of 5% (and + 5% of additional patients). The number of patients required is 340 in each cohort, for a total of 680 patients.

- For each cohort, an unblinded interim analysis will be performed when 30% of the patients of the first stage reach the primary endpoint [102 patients]. The aim of this analysis is to reestimate the sample size of the trial. If the conditional power for detecting the difference in primary outcome between the two arms in the final analysis is between 50% and 90%, the sample size will be increased in order to achieve 90% power to detect the effect observed at the interim analysis, with a maximum sample size of 1020 per cohort. Otherwise, the trial will continue using the planned sample size.

It was decided to conduct an open trial because transfusion of plasma without neutralizing antibodies generates a risk without any benefit for the placebo arm.

